### Summary of findings from pertinent pre-clinical studies and clinical trials

Statins offer the opportunity to improve outcomes in the treatment of rectal cancer. A Danish population study of 295,925 cancer cases of all types revealed that the use of statins significantly improved overall survival (OS) and specifically in those with CRC (HR 0.79, 95% CI 0.74–0.85) [9]. Similarly, a registry study of 10,762 CRC patients from Taiwan reported that, on multivariate analysis, cancer-specific survival was independently and significantly improved in statin users (HR 0.72 *p* < 0.001) [10]. More recently a population-based cohort study of 7657 patients with CRC in the United Kingdom showed that statin use improved cancer-specific survival (HR, 0.71; 95% CI, 0.61–0.84) and all-cause mortality (HR, 0.75; 95% CI, 0.66–0.84) [11].

Preclinical studies have elaborated effects on cell signalling pathways that may contribute to better cancer outcomes with statins, many of which are independent of cholesterol metabolism [12]:
generation of pro-apoptotic, growth-inhibitory and pro-differentiation responses in tumours;inhibition of angiogenesis, invasion and metastasis;reducing inflammation and inhibiting radiation (RT)-induced gut and skin toxicities while radiosensitising tumour cells and maintaining tumour control compared to RT alone [13–20].

This correlates with retrospective clinical studies in which patients taking statins during RT or chemo-RT for rectal, bladder or prostate cancer had significantly higher rates of pathological complete response (CR), local control and progression-free survival, respectively [21–25]. The findings in three published retrospective studies using pCRT in rectal cancer patients were:
in 407 patients at the Cleveland Clinic, favourable pathological regression was seen in 65.7% of statin users vs. 48.7% of others, *p* = 0.004 (multivariate OR 2.25; 95% CI 1.33–3.82) [22].multivariate analysis of 891 Canadian patients from multiple centres showed a significantly higher pathological CR rate in statin users (OR 1.7, 95% CI 1.04–2.89, *p* = 0.044) [23];in 349 patients from Memorial Sloan-Kettering Cancer Center pathological CR was higher in statin users (30% vs. 17%), with multivariate OR 4.2 (95% CI 1.7–12.1; *p* = 0.003) [24].

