#### Translational endpoints

This trial is an important opportunity to identify whether assessment of systemic inflammation (reflected in the modified Glasgow prognostic score, mGPS) and the local inflammatory response (through characterising infiltrating lymphocytes) could be an important translational research component of a subsequent phase III trial of statins in rectal cancer patients. Additionally, it will allow us to evaluate the impact of SIM on the relationship between specific T-cell infiltrates in pre-pCRT biopsies and pathTRG in the resected tumours, and with normal tissue inflammation post-pCRT.

It is long-recognised that a local inflammatory response with infiltration of T-lymphocytes into CRC carries a better prognosis, independent of tumour stage [50, 51]. Conversely preoperative systemic inflammation, reflected in the blood neutrophil/lymphocyte ratio (NLR) or serum c-reactive protein (CRP) and albumin levels (summarised in the modified Glasgow Prognostic Score), correlates with worse prognosis, independent of stage and preoperative therapy [52]. This adverse prognostic relationship persists with elevated mGPS 3–6 months postoperatively [52]. While statins are anti-inflammatory [12] and reduce the NLR in patients with high cholesterol [53], it is not known whether they lower the NLR or mGPS in cancer patients.

The Immunoscore is a recently-validated test that characterises T-cell subsets infiltrating into the centre of the tumour and at the invasive margin of CRC by immunohistochemistry (IHC) for CD3 and CD8; higher scores correlate with a lower risk of relapse and improved DFS and OS, independently of stage [54, 55]. While the Immunoscore was validated in rectal cancer patients who had primary surgery, it cannot be applied to those patients who received pCRT because identification of central and margin regions is compromised due to tumour regression and fibrosis [56]. However, in diagnostic rectal biopsies taken prior to pCRT prominent infiltration of CD3+ and CD8+ T-cells strongly correlated with pathological CR rates following pCRT (56).

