A number of correlative/translational objectives are intended. We aim to determine in the total trial population: 1) The association between mrTRG and pathTRG grouping (association between mrTRG and pathTRG grouping); 2) The inter-observer agreement between site radiologists and a central radiologist on mrTRG scoring (inter-observer agreement on mrTRG scoring); 3) The inter-observer agreement between site pathologists and a central pathologist on pathTRG scoring (inter-observer agreement on pathTRG scoring). In addition we aim to compare between the SIM and placebo groups treated with pCRT: 1) The association between CD3+ and/or CD8+ T-cell infiltrates in the tumour in the pre-pCRT diagnostic biopsies and pathTRG (association between T cell infiltrates and pathTRG); 2) the intensity and distribution of subsets of infiltrating T-cells in irradiated normal and malignant tissue in the resected specimen; 3) The influence of SIM on systemic inflammation, assessed with the mGPS and the NLR (mGPS and NLR).

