### Surgery

Patients will undergo resection of their rectal cancer at a time recommended by their surgeon (generally 7–10 weeks after completion of pCRT). Patients with an excellent clinical and radiological response may be observed under a “watchful waiting” programme if agreed with their surgeon.

Surgery may include open, laparoscopic, robotic or transanal total mesorectal excision approach. This will include both restorative low anterior resection, or abdomino-perineal resection with permanent end-colostomy.

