### Statistical methodology

#### Sample size

The primary endpoint of this trial is rates of favourable mrTRG (grades 1 or 2). This will be analysed using ordinal regression with 4 ordered categories of mrTRG (1, 2, 3 and 4–5) to provide greater sensitivity. Based on published data using MRI 6–8 weeks after pCRT, the expected rate of mrTRG in the control group is 9% grade 1, 39% grade 2, 20% grade 3 and 32% grades 4–5. A 35% relative increase in favourable mrTRG would be a worthwhile difference to inform a phase III trial.

Based on an ordinal proportional odds assumption, a sample size of 222 patients (111 treated with SIM and 111 controls) will have > 80% power to detect a change in mrTRG rates to 17% grade 1, 48% grade 2, 16% grade 3 and 19% grades 4–5 with 95% confidence.

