#### Statistical analysis

Intention-to-treat analysis of results will be the primary analysis. In addition, an exploratory per protocol analysis will also be conducted which will exclude ineligible patients, those not taking trial medication when starting pCRT and those who withdraw their consent to participate prior to response evaluation.

The primary endpoint and all secondary endpoints expressed as proportions will be estimated, together with corresponding 95% confidence intervals based on exact binomial distributions. Kaplan-Meier curves will be calculated for all time-to-event endpoints. Rates at specific points in time (e.g. 3-year local recurrence rate) will be estimated from these Kaplan-Meier curves.

Inter-observer agreement is defined as the degree of agreement in mrTRG (or pathTRG) results when reviewed by the central radiologist (or pathologist) and the reporting site radiologists (or pathologists). Results for each of mrTRG and pathTRG will be reported separately in a 3X3 grid comparing favourable, intermediate, and unfavourable scores between central and site radiologists and pathologists respectively. Inter-observer agreement will be assessed using a weighted kappa statistic > 0.40 is defined as moderate agreement. This will be assessed for mrTRG after recruitment of 35 randomised patients to ensure procedural consistency and again at the conclusion of the trial.

Adverse events in each arm will be tabulated and graded according the NCI CTCAE version 4.03.

For analysis of translational objectives, association between CD3+ and CD8+ T-cell infiltrates in diagnostic rectal cancer biopsies and pathTRG following pCRT will be evaluated using the chi-square test for trend. The effect of SIM on subsets of T-cells in tumours and normal tissue will be evaluated by comparison of distribution of scores for each cell type in SIM and placebo groups using the chi-square test for trend. Changes in the NLR and mGPS over time will be analysed using repeated measures ANOVA.

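### The simvastatin-versus-placebo comparison of T-cell scores in malignant resected tissue exists only for patients with residual tumour, so it is not a randomised comparison and cannot show simvastatin's effect

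*Protocol article*

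**What the plan says.** The translational objectives (Methods/design) include a comparison between the simvastatin and placebo groups of "the intensity and distribution of subsets of infiltrating T-cells in irradiated normal and malignant tissue in the resected specimen". The Statistical analysis section turns this into a test of drug effect: "The effect of SIM on subsets of T-cells in tumours and normal tissue will be evaluated by comparison of distribution of scores for each cell". Both groups enter a chi-square test for trend. It does not say how a patient without residual tumour enters the tumour part of the comparison.

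Three other statements bear on this:

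- Translational endpoints reports that in diagnostic biopsies taken before preoperative chemoradiation (pCRT), "prominent infiltration of CD3+ and CD8+ T-cells strongly correlated with pathological CR rates following pCRT".
- The same section says the Immunoscore cannot be applied after pCRT because "identification of central and margin regions is compromised due to tumour regression and fibrosis".
- The Surgery section allows some patients to have no specimen: "Patients with an excellent clinical and radiological response may be observed under a “watchful waiting” programme if agreed with their surgeon".

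**The concern.** The tumour part of the objective needs malignant tissue after pCRT. A resected patient with complete response has none. Whether a patient has residual tumour is settled after randomisation, and moving that outcome is the purpose of the trial. If simvastatin works as hoped, fewer simvastatin than placebo patients will have a tumour to score, and those left need not be comparable between arms. The article's own link between CD3+/CD8+ infiltrates and complete response makes it credible that the lost tumours differ in the quantity being measured.

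At stake is what the trial may say about local T-cells. A difference in residual tumour could arise without any drug effect on T-cells, or a real one could be masked. The Overall purpose section says a finding on the local inflammatory response, together with the systemic markers, would inform whether such work is included in a phase III trial. The primary endpoint is not touched.

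**Working it through.** **The plan's own figure.** No size or power is given for the T-cell comparison. The only power statement is for the primary endpoint. The control distribution is given as "the expected rate of mrTRG in the control group is 9% grade 1, 39% grade 2, 20% grade 3 and 32% grades 4–5", and the trial is sized "to detect a change in mrTRG rates to 17% grade 1, 48% grade 2, 16% grade 3 and 19% grades 4–5 with 95% confidence". The odds ratio at the favourable cut is (0.65/0.35)/(0.48/0.52) = 2.01. Mean category proportions are 0.13, 0.435, 0.18 and 0.255, so 1 − Σp̄³ = 0.893. The proportional-odds formula N = 12(1.96 + 0.842)² / [ln(2.01)² × 0.893] gives 216 for 80% power. With 222 patients, power is about 81% (79.7% by simulated rank test). The stated figure reproduces. The design alternative thus expects grade 1 regression to rise from 9% to 17%, so the arms are expected to differ in who has residual tumour.

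**Scorable tumours, if all 111 per arm are resected.**

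- CR 17% versus 30% (a retrospective cohort in the Background): 111 × 0.83 = 92 versus 111 × 0.70 = 78.
- CR 9% versus 17% (mrTRG grade 1 as a stand-in): 111 × 0.91 = 101 versus 111 × 0.83 = 92.

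**Bias with no drug effect on T-cells, model 1.** Infiltrate density and latent response are bivariate normal with assumed correlation ρ, the same in both arms. Residual tumour means response below the (1 − CR) quantile t. Mean density among residual tumours is −ρφ(t)/Φ(t).

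- 17% versus 30%: t = 0.954 and 0.524; φ/Φ = 0.305 and 0.497; arm difference −0.192ρ. For ρ = 0.3, 0.5 and 0.7 this is −0.06, −0.10 and −0.13 SD. With standard errors of about 0.15, 0.145 and 0.136 SD, the two-sided 5% test rejects in about 7%, 10% and 17%.
- 9% versus 17%: φ/Φ = 0.178 and 0.305; arm difference −0.126ρ, or −0.04, −0.06 and −0.09 SD; rejection about 6%, 7% and 10%.

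**Model 2, which allows the biopsy link to fade or differ by arm.** Pre-treatment infiltrate x is standard normal. CR follows a logistic model with log-odds slope β per SD, its intercept set to give the arm's CR rate. The resected score has correlation ρ with x and no drug effect. Entries are simvastatin minus placebo in SD, with the false-positive rate from a normal test as a proxy for the trend test.

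| Scenario | CR 17% vs 30% | CR 9% vs 17% |
|---|---|---|
| β = 1 both arms, ρ = 0 | 0.00 (5%) | 0.00 (5%) |
| β = 1 both arms, ρ = 0.3 | −0.03 (5%) | −0.02 (5%) |
| β = 1 both arms, ρ = 0.5 | −0.05 (6%) | −0.03 (6%) |
| β = 1 both arms, ρ = 1 | −0.10 (10%) | −0.07 (7%) |
| No link, ρ = 0.5 | 0.00 (5%) | 0.00 (5%) |
| Inverse link both arms (β = −1), ρ = 0.5 | +0.05 (6%) | +0.03 (6%) |
| Weaker on simvastatin (β = 1 vs 0.3), ρ = 0.5 | +0.03 (5%) | +0.02 (5%) |
| Absent on simvastatin (β = 1 vs 0), ρ = 0.5 | +0.07 (8%) | +0.04 (6%) |
| Reversed on simvastatin (β = 1 vs −0.5), ρ = 0.5 | +0.14 (16%) | +0.08 (9%) |

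The values of ρ and β are assumptions; the article gives none. The sign depends on the mechanism.

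**The case against.** The strongest reply has four parts.

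- **Condensation.** How specimens without residual tumour are scored is pathology-manual or analysis-plan detail that an article leaves out, and nothing says complete responders are dropped. This stands as far as the absent handling rule goes. It does not answer the main point: the stated target is malignant tissue and the stated reading is an effect of simvastatin. No rule in a fuller document can supply malignant tissue where there is none.
- **Direction.** A reader might infer that better response on simvastatin must make its T-cell scores look lower. The documents do not support that. The association with CR is reported for CD3+ and CD8+ cells in biopsies before pCRT. Nothing relates infiltrate in resected tissue to response, and no link between regulatory T-cells and CR is given. If simvastatin's additional complete responses come from tumours with few T-cells, the remaining scores look higher. This objection stands in full.
- **Size.** The 17% versus 30% contrast comes from the cohort with the largest odds ratio cited for CR (4.2). Another cohort has 1.7, and a New Zealand study showed no improvement in CR; with equal CR rates and the same link in both arms, these models give no bias. This also stands, so the figures are illustrations and mostly small.
- **Weight.** The objective is tertiary, and the article says its results would inform phase III, not decide it. That limits the importance but does not make the comparison randomised.

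A reader might also take the remark on central and margin regions to rule out all spatial scoring after pCRT. It concerns the Immunoscore, which the objective does not propose to use.

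**Conclusion.** The structural point holds. The malignant-tissue comparison conditions on residual tumour, which simvastatin is meant to change, so it cannot be read as the drug's effect on tumour T-cells. This needs only the stated objective and the absence of malignant tissue in complete responders.

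Neither the sign nor the size of bias can be fixed from the documents. With CR of 17% versus 30% it runs from 0 to about 0.13 SD toward lower scores on simvastatin when the link is positive and equal in both arms, and reaches about 0.14 SD toward higher scores if the link reverses on simvastatin. With 9% versus 17% it is about 0.02 to 0.09 SD in either direction where a link exists, and zero where none does. Against standard errors of about 0.14 to 0.15 SD these are modest shifts. The defect lies more in what the trial may conclude than in a large error rate. Irradiated normal tissue is not lost through complete response in resected patients, but it too is limited to those resected.

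**What to change.** In the Statistical analysis section and the translational analysis plan:

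1. State that the arm comparison of T-cell subsets in malignant tissue is descriptive and conditional on residual tumour.
2. Report by arm the number of randomised patients with no scorable tumour, separating pathological complete response from no resection.
3. Rest any statement about simvastatin's effect on local T-cells on irradiated normal tissue, noting that it covers resected patients only.
4. Add, as a supportive analysis, a tumour-bed score in all resected patients, complete responders included.

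Spatial scoring need not be dropped. Complete response need not become a level of the ordered trend test; it has no natural rank on a T-cell scale, and a difference could then reflect response and not T-cells.

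The cost is wording and an extra entry on the scoring sheet, using the same resected specimens. The price in interpretation is a weaker claim for tumour tissue, and tumour-bed scores that are less specific than scores in viable tumour.

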### Post-operative management

Treatment after discontinuation of trial treatment is at the discretion of the patient’s clinician. Adjuvant chemotherapy may be administered on the recommendation of the treating clinician and its use will be recorded.

Blood tests will be performed on the first day of pCRT, prior to starting chemotherapy, to assess the impact of trial medication on the mGPS and NLR. Clinical assessments including IBDQ-B questionnaire will be conducted on Trial Weeks 3, 5 and 7 [62].

Week 13 assessments will be performed 6 weeks (+/− 7 days) after completion of pCRT and prior to surgery. An MRI scan for mrTRG must be completed 6–8 weeks after completion of pCRT and must be prior to surgery. The postoperative visit will include assessment of length of hospital stay after surgery and any readmission data. Subsequent follow-up is annually.

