### Data to be collected

The study will collect data on: baseline patient and tumour status; treatment delivery; baseline and post-pCRT MRI assessments; clinical and laboratory toxicity assessments; baseline and resection histopathology; followup data for PFS and OS (Table 1).

**Table 1 Tab1:** Schedule of Assessments

Treatment Period – Trial Week											
	Baseline / screening	1	2	3	4	5	6	7	13	4–6 weeks post-op	Follow up
Informed consent	X										
History	X									X	
Physical exam ^b^	X			X		X		X		X	
Trial medication start		X									
Preoperative CRT			X	X	X	X	X	X			
Concomitant meds	X			X		X		X	X		X
Trial med compliance				X		X		X	X		
Adverse events				X		X		X	X		X
Haematology	X		X	X	X	X	X	X	X		
Chemistry incl. CRP	X		X	X	X	X	X	X	X		
CEA	X										X
Serum pregnancy test	X										
Resected rectal tissue										X	
CT scan	X										X
Pelvic MRI	X								X ^o^		
Lower GI endoscopy	X										X

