## Discussion

Little progress has been made in the management of T3 rectal cancer in the last 10 years. The findings in several retrospective studies that statin use in patients undergoing pCRT appears to confer higher pathological regression rates, more pathological CR [22–24] and also lower RT toxicity [16, 22–24], led us to mount this phase II RCT. We chose to start statin therapy 1 week prior to pCRT to observe for clinical and biochemical effects independent of pCRT, and continue it for 3 months to allow maximum interaction with CRT. The use of a standard dose of simvastatin is pragmatic; 40 mg per day is the highest dose that is well tolerated. The evaluations are comprehensive, including comparative treatment-induced changes in MR scans, pathological evaluation of the resected specimen, and blood biochemical changes, as well as longer-term tumour outcomes (PFS and OS). With this sample size of 222 patients (111 simvastatin and 111 placebo), we should be able to observe meaningful differences in these parameters if simvastatin has any beneficial effect in the treatment of this disease.

If this study has a positive result, a larger RCT will be needed to confirm and validate the merit of statins in the preoperative management of rectal cancer, especially long-term clinical outcomes. Such a finding could also lead to studies of statins in conjunction with radiation and chemotherapy in a range of other malignancies, as well as further exploration of possible mechanisms of action and interaction of statins with both radiation and chemotherapy. The translational substudies undertaken with this trial will provisionally explore some of these possible mechanisms, and the tissue and data can be made available for further investigations.

This trial is an important opportunity to identify whether assessment of systemic inflammation (reflected in the neutrophil-lymphocyte ratio and the mGPS) and the local inflammatory response (through characterising infiltrating immune cells) could be important translational research components of a subsequent phase III trial of statins in rectal cancer patients. Additionally, it will allow us to evaluate the impact of SIM on the interaction of specific T-cell infiltrates in pre-pCRT biopsies with pathTRG in the resected tumours, and with normal tissue inflammation after pCRT.

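### Repeated measures ANOVA for NLR and mGPS names no baseline-adjusted arm comparison at the pre-chemoradiation sample, and fits a model for means to a score (minor)

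*Protocol article*

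**What the plan says.** The translational objectives (Methods/design) pose a between-arm question: "The influence of SIM on systemic inflammation, assessed with the mGPS and the NLR". The Statistical analysis section answers it with one sentence covering both markers: "Changes in the NLR and mGPS over time will be analysed using repeated measures ANOVA".

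Two other places give one blood sample a particular role. Under Post-operative management: "Blood tests will be performed on the first day of pCRT, prior to starting chemotherapy", and the reason given is "to assess the impact of trial medication on the mGPS and NLR". The Discussion explains the lead-in: "We chose to start statin therapy 1 week prior to pCRT to observe for clinical and biochemical effects independent of pCRT".

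Table 1 (Data to be collected) marks haematology and the row "Chemistry incl. CRP" at baseline, weeks 2 to 7 and week 13, which is eight draws. Trial medication starts in week 1 and chemoradiation in week 2, so the week 2 draw, taken before chemotherapy, is the only one on trial drug that chemoradiation has not yet affected.

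On the type of measure, the Translational endpoints section describes mGPS as a summary of two laboratory values: "serum c-reactive protein (CRP) and albumin levels (summarised in the modified Glasgow Prognostic Score". NLR is a ratio. Elsewhere the article respects the order of graded outcomes: mrTRG is analysed by ordinal regression in four categories (Sample size), and T-cell scores by a chi-square test for trend (Statistical analysis).

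**The concern.** The sentence fixes a method, so this is a choice made in the document and not a detail left to the SAP. An SAP that follows it inherits the difficulty, and one that departs from it contradicts the protocol.

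- **Target.** A test of change over time is not, as worded, a test of simvastatin against placebo. Even read as an arm-by-time test, it spreads the first-day comparison over a profile in which six of the eight samples fall during or after chemoradiation. No baseline-adjusted comparison is named at the sample said to serve that purpose.
- **Scale.** A model for means is a poor match for a score, and mGPS is handled differently from the article's other graded outcomes.
- **Incomplete series.** In its classical form the method uses only patients with every sample.

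The article says these markers may inform the translational content of a phase III trial (Translational endpoints, Overall purpose). A diluted test could lead to a useful marker being dropped.

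**Working it through.** **The plan's own figure.** The article gives no power or precision for NLR or mGPS. Its one design figure, more than 80% power for mrTRG with 111 per arm, reproduces: about 81.7% by the Whitehead formula at odds ratio 2.03, and 81.4% by Wilcoxon simulation. It does not bear on this point.

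**Inputs.** From the article: 222 patients, 111 per arm; eight scheduled samples. Read as two-sided: 5% significance. Assumed: everything about the distribution of NLR and mGPS, the correlation between visits, the effect size and the rate of missing samples.

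**1. One contrast against an omnibus test.** For 80% power on 1 degree of freedom, the noncentrality is (1.96 + 0.84)² = 7.85. With eight samples an arm-by-time test has 8 − 1 = 7 degrees of freedom, and the 5% critical value of chi-square is 14.07. P(noncentral chi-square with 7 df and noncentrality 7.85 > 14.07) = 0.493. So 80% falls to about 49%, provided the whole effect lies in that one contrast.

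**2. Illustration on log NLR.** Assume log SD 0.5 at baseline and week 2, rising to 0.7 during chemoradiation, correlation 0.8 per two weeks, and an effect of −0.15 log units. For the baseline-adjusted week 2 comparison:

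- residual SD = 0.5 × √(1 − 0.8²) = 0.30
- standard error = 0.30 × √(2/111) = 0.0403
- 0.15/0.0403 = 3.72, and Φ(3.72 − 1.96) = 0.96

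Simulation (2,000 runs per scenario, no missing data) gave:

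| Effect | Week 2 ANCOVA | ANOVA, arm | ANOVA, arm × time (Greenhouse-Geisser) |
|---|---|---|---|
| Week 2 only | 96% | 6% | 29% |
| Sustained from week 2 | 96% | 50% | 33% |

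On untransformed NLR the two ANOVA figures were 5% and 5% for the week 2 effect, and 44% and 24% for the sustained effect. The gap depends on the assumed correlation and variances, so it shows direction and not size.

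**3. mGPS.** On assumed splits over three levels, adjustment for baseline gave about 74–84% power for a sustained effect, against 49–56% for the plain arm test.

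**4. Complete series.** With samples missing independently at rate m per visit, the share of patients with all eight is (1 − m)⁸, and with baseline plus week 2 it is (1 − m)²:

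| m (assumed) | All eight, of 222 | Baseline + week 2, of 222 |
|---|---|---|
| 2% | 189 (85%) | 213 (96%) |
| 5% | 147 (66%) | 200 (90%) |
| 10% | 96 (43%) | 180 (81%) |

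**5. Type I error.** With no treatment effect, the arm test on NLR rejected in about 5% of runs, on both the raw and the log scale. For mGPS on the assumed splits it rejected in about 5–6%. The uncorrected arm-by-time test rejected in about 10–11% for NLR and 7–8% for mGPS, because sphericity fails under the assumed correlation. With Greenhouse-Geisser both returned to about 4–5.5%.

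**The case against.** Much can be said for the plan.

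- **The trial's purpose.** A reader might infer that the trial was built around the first-day sample. It was not. It is sized for mrTRG, and the Overall purpose section also asks whether adding simvastatin to chemoradiation alters systemic inflammation, so the later samples serve a stated aim. What stands is narrower: the article gives the first-day sample a purpose and no matching comparison.
- **Wrong p-values.** A reader might infer that ANOVA on a score or a skewed ratio gives invalid tests. The check does not show that at 111 per arm; the exception is the arm-by-time test without a sphericity correction, which is routine to apply.
- **Dropped patients.** No complete-case rule is stated, and the term repeated measures ANOVA is sometimes used for mixed models that keep partial data. Missing-data handling may sit in the full protocol or SAP. The loss is therefore conditional on the classical form.
- **Undocumented inputs.** The article gives neither the mGPS levels nor a distribution for NLR, so skewness is plausible but not documented. Nor does it say that all eight draws enter the analysis.
- **The 49% figure.** It describes one extreme scenario, while the drug is taken for 90 days. A planned contrast inside the repeated measures model would recover the comparison, and the article does not exclude one.

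These objections limit the size of the point and rule out the stronger readings. They do not supply the missing comparison or explain why mGPS is treated differently from the other graded outcomes.

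**Conclusion.** The point holds in limited form and is minor. The named method is a model for means applied to a score, out of line with the article's own ordinal and trend analyses. It also states no baseline-adjusted arm comparison at the sample intended to show simvastatin's effect apart from chemoradiation. The consequence is a possible loss of power, with 80% falling to about 49% as a limiting example, and smaller or larger losses under other assumptions. Loss of patients, about a third at an assumed 5% missing per visit, follows only if classical ANOVA is used on all eight samples. Only a translational objective is affected; the primary endpoint and the sample size are not.

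**What to change.** In the Statistical analysis section, replace the sentence on NLR and mGPS with three parts:

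- a planned comparison of simvastatin with placebo on log NLR at the first day of chemoradiation, adjusted for baseline log NLR;
- a likelihood-based mixed model for log NLR over all available visits, with baseline, arm, visit and arm-by-visit terms, to describe the course during and after chemoradiation;
- a proportional-odds longitudinal model for mGPS, with its levels stated.

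No new data are needed. The cost is a little more analysis work and reliance on the proportional-odds assumption for mGPS, which the article already accepts for mrTRG.
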